**Methods/design:**

Participants with SAD (*N* = 128), will be recruited from the general population. A composite score combining the scores obtained from three social anxiety questionnaires will serve as the primary outcome measure. Secondary measures include self-reported depression and quality of life. All treatments and assessments will be conducted via the Internet and measurement points will be baseline, Week 2, post-treatment, and 4 months post-treatment.

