### Sample size

Effect sizes of the difference between ICBT plus attention training and ICBT plus control training are difficult to estimate. First, in previous trials, the pure comparison of attention training versus control training resulted in varied controlled effect sizes between *d* = −0.07 and 1.59 [34,40]. Second, ICBT alone yielded large effect sizes of *d* = 0.70 to 1.38 compared to a waiting-list control (e.g.[11,52]). The combination of these two approaches has not yet been evaluated systematically. By considering clinical relevancy, we based our sample size calculation on a medium controlled effect size. On the basis of a controlled effect size of *d* = 0.50 in a two-sided *t*-test (α = 0.05, power 80%) comparing ICBT plus attention training with ICBT plus control training, the sample size, *N*, will be set at 128 participants, with 64 participants in each group.

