### Outcome measures

We will use a composite score of the following three self-report measures of social anxiety as primary outcome measure: the self-report version of the Liebowitz Social Anxiety Scale [53], the SPS, and the SIAS [54]. In addition, as secondary outcome measures, we will administer the MADRS-S to assess depressive symptoms [50], and the Quality of Life Inventory [55]. To monitor the progress of social anxiety during the attention and control training exercises, we will administer the Mini-SPIN, a three-item screening measure, prior to each attention or control session [64].

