### Statistical analysis

All analyses of primary and secondary outcome measures will be conducted as intention-to-treat analyses (ITT). Depending on the amount of drop-out, the ITT analyses will be carried out either as mixed models or using the ‘last observation carried forward’ method. Social anxiety measures will be integrated in a social anxiety composite following the procedure recommended by Rosnow and Rosenthal [65] and applied by Clark *et al.*[66]. The composite score will be generated by converting each social phobia scale across all assessment points to *z*-scores, and then by averaging across the measures. Between-group changes at post-treatment and at 4-month follow-up on the social anxiety composite and on secondary outcome measures will be calculated using analysis of covariance (ANCOVA), with pre-treatment scores as the covariate. Effect sizes between and within the two groups will be calculated with Cohen’s *d* computed with the pooled standard deviation.

Clinically significant change at post- and follow-up assessment will be estimated for the LSAS-SR, the SIAS, and the SPS. In accordance with Jacobson and Truax [67], we will calculate the proportion of improved and recovered participants using the Reliable Change Index and cut-off scores based on the Jacobson and Truax’s formula, *c*.

The attention-bias assessment will produce reaction times for each participant to three kinds of negatively cued trial (positive–negative, neutral-negative, positive-neutral) and to three kinds of positively cued trial (positive–negative, neutral-negative, positive-neutral). We will calculate the mean reaction time for each participant for positively cued and negatively cued trials, eliminating response latencies for inaccurate trials and response latencies less than 200 ms or greater than 2000 ms. To examine changes in attention bias, we will conduct a 2 (pre-assessment/post-assessment) × 2 (attention training/control condition) × 2 (positive/negative) analysis of variance (ANOVA). Furthermore, we will analyze changes in the attention bias from pre- to post-assessment on an individual level using an attention bias score. We will calculate this bias score by subtracting the mean reaction times to negative cues from the mean reaction times to positive cues. Positive individual bias scores will indicate biased attention towards threat. Negative bias scores will indicate biased attention away from threat.

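### The primary composite has no named primary time point: the same ANCOVA is planned at post-treatment and at 4 months, unranked, while the sample size covers one test

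*Protocol article*

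**What the plan says.** Outcome measures (protocol article) defines the primary outcome by instrument only: "We will use a composite score of the following three self-report measures of social anxiety as primary outcome measure". No time point is attached there, in the abstract, or in the hypothesis that closes the Background, which says only that the attention-training group will do better on social anxiety measures.

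The abstract lists the occasions: "measurement points will be baseline, Week 2, post-treatment, and 4 months post-treatment". Statistical analysis selects two of them for the between-group ANCOVA, with the pre-treatment score as covariate: "Between-group changes at post-treatment and at 4-month follow-up on the social anxiety composite and on secondary outcome measures". Both occasions appear in one sentence and receive the same test. The article gives no order of testing, no adjustment and no rule for success.

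Sample size rests on one comparison. It starts "On the basis of a controlled effect size of *d* = 0.50" and continues "in a two-sided *t*-test", with the design values "α = 0.05, power 80" (per cent), "comparing ICBT plus attention training with ICBT plus control training". The total "will be set at 128 participants, with 64 participants in each group". It does not say on which occasion that comparison is made.

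**The concern.** A primary endpoint needs a variable, a time point and a comparison. The article fixes the variable and the comparison, and offers two time points without choosing. The sample size presupposes that the choice has been made, because it budgets 5% for one test.

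Two things are at stake. First, whoever reads the results can treat a significant difference at either occasion as support for the hypothesis, and the 5% in the sample-size paragraph would then not describe the error rate of that claim. Second, and more important in practice, a mixed result has no agreed meaning. A difference at Week 11 that has gone by 4 months, or one that appears only at 4 months, could be reported as success or as failure. The Discussion says that success here and in replications would argue for building the training into Internet-based and face-to-face therapy, so what counts as success should be settled before the data are seen.

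**Working it through.** **Inputs from the article.** Sample size: d = 0.50 (SD 1 on the standardised scale), two-sided alpha 0.05, power 80%, 64 per group. Statistical analysis: two occasions tested on the composite. Week 2 is a measurement point, but no between-group ANCOVA is planned for it, so it is not counted.

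**Input not in the article.** The correlation ρ between the two test statistics. The same participants are measured twice, so it should be positive. I assume 0.5 to 0.9 and give independence as an upper reference.

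**Step 1: the plan's own figure.** Normal approximation: n per group = 2(1.960 + 0.842)² / 0.50² = 62.8, so 63 per group (126 in total). The noncentral t solution is 63.77, so 64 per group and 128 in total. Power at 64 per group is 80.1%. The stated figure is reproduced exactly, for one test.

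**Step 2: error if either occasion may carry the claim.** With no true difference at either occasion:

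- Two-sided: 1 − P(|Z₁| < 1.96, |Z₂| < 1.96). If independent, this is 1 − 0.95² = 9.75%.
- In favour of attention training only: 1 − P(Z₁ < 1.96, Z₂ < 1.96). If independent, this is 1 − 0.975² = 4.94%, against a nominal 2.5% for one test.

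Bivariate normal probabilities give:

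| ρ (assumed) | Two-sided error | Error favouring attention training |
|---|---|---|
| 0 (independent) | 9.75% | 4.9% |
| 0.5 | 9.1% | 4.5% |
| 0.7 | 8.4% | 4.2% |
| 0.8 | 7.8% | 3.9% |
| 0.9 | 7.0% | 3.5% |

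**Step 3: if both occasions had to be significant.** Type I error is not inflated. With d = 0.50 at both occasions and the unadjusted comparison used for sizing, the noncentrality is 0.50 × √(64/2) = 2.83 at each, and the probability that both are significant is about 70% (ρ = 0.5) to 76% (ρ = 0.9). That is below the stated 80%. Baseline adjustment would raise it by an amount the article's figures do not determine.

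**Step 4: under the repair.** With one named occasion there is one test at 5%, and the 128 participants and 80.1% power from Step 1 apply to it. In a fixed sequence the second test is made only after the first is significant, so familywise error stays at or below 5% with the same N.

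**The case against.** **The article is condensed, and a separate analysis plan may deal with multiplicity.** This stands for an adjustment method or a testing hierarchy, whose absence here is no fault. It does not stand for the time point. That belongs to the definition of the primary outcome and to the basis of the sample size, both of which the article sets out.

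**The wording leans towards post-treatment.** The hypothesis concerns treatment outcome, the later occasion is called a follow-up, and the trial is sized for one test. This is a fair reading, and probably the intended one, but it is not a designation: the analysis sentence treats both occasions alike.

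**No either/or rule is stated.** This stands. A reader might infer that the two occasions are co-primary, that testing is deliberately unadjusted, and that the 5% level is therefore breached. The article says none of these things; they would be read from its silence. The percentages in Step 2 hold only if success at either occasion is accepted.

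**The two-sided figure overstates the matter.** This stands in part. The hypothesis is directional, and about half of the 7.0% to 9.1% consists of false results favouring control, which could not support it. For the claim the trial wants to make, the relevant figure is the 3.5% to 4.9% against 2.5%.

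**Splitting alpha.** A reader might argue that testing each occasion at 0.025 would cut power from 80% to 71%, so that naming one occasion is the only affordable course. The 71% (71.2% at 64 per group) is for an unadjusted t-test, whereas the plan analyses by baseline-adjusted ANCOVA. Dividing d by √(1 − r²) gives about 76% to 90% at alpha 0.025 for assumed baseline–outcome correlations r of 0.3 to 0.6. The case for naming one occasion therefore does not rest on that loss.

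**Conclusion.** The point holds as a defect in how the primary endpoint is fixed. The composite is primary, two occasions are tested identically, neither is ranked, and the sample size covers one test. The sample-size arithmetic itself is right.

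The size of any error inflation is conditional on an either/or reading that the article leaves open but does not state, and on an assumed correlation between the test statistics. Under that reading every value in the assumed range exceeds the nominal level, in both columns of the table. Under the opposite reading, with both occasions required, there is no inflation, but the stated 80% power no longer describes the trial's chance of success. The lack of a prespecified interpretation for a mixed result depends on neither assumption.

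**What to change.** Before unblinding, add to Outcome measures and Statistical analysis, and refer to it in Sample size, a statement such as: the primary endpoint is the between-group difference in the social anxiety composite at post-treatment (end of Week 11), estimated by ANCOVA adjusted for the pre-treatment score and tested two-sided at 5%; the comparison at the 4-month follow-up is secondary. If a confirmatory claim at 4 months is wanted, state instead that it is tested at 5% only if the post-treatment comparison is significant.

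The cost is one sentence. No assessment, participant or analysis is added. The small downside is that the 4-month result becomes secondary or gated, so a difference seen only at 4 months could not by itself support a confirmatory claim.

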**Discussion:**

There is no direct evidence of the effects of combining CBM and ICBT in SAD. Adding attention-training sessions to ICBT protocols could increase the proportion of participants who improve and recover through Internet-based self-help.

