First studies on the predictive value of attention bias in cognitive-behavior therapy show that individuals with a pronounced attention bias benefit less from CBT for SAD. Legerstee *et al*. [43] and Price *et al*. [44] both showed that greater attention-bias scores prior to the intervention were associated with higher post-treatment anxiety scores in CBT. Pishyar *et al*. [45] and Lundh and Öst [46] found that CBT interventions reduced biases in attention processes in individuals with SAD and that this reduction of the attention bias was associated with changes in social anxiety. These findings imply that a combination of attention training and CBT could be beneficial in reducing symptoms of SAD. Even if CBT manuals do not focus explicitly on the attention bias, patients are encouraged to process all social cues (negative, positive, and neutral) in exposure exercises and behavioral experiments. As Rodebaugh *et al*. [5] concluded, all therapies for SAD share the assumption that change will occur through the experience of a social situation as it, “is actually like, as opposed to how clients fear or think it will be.”

Until now, there has been no direct evidence of the advantages of combining attention training with CBT in SAD. However, Amir and Taylor [47] showed promising results in a small study targeting generalized anxiety disorder. Adding attention-training sessions to ICBT protocols could increase the proportion of participants who improve and recover through Internet-based self-help.

This study aims at evaluating the combination of attention training and Internet-based cognitive-behavioral therapy (ICBT). It is designed to compare two groups, one group receiving ICBT and attention training towards threat cues and one group receiving ICBT and control training. We hypothesize that the group receiving ICBT plus attention training will show a better treatment outcome on social anxiety measures than the control group.

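### If LOCF is used, the post-treatment improved and recovered proportions classify anyone missing Week 11 on a score taken before any CBT module

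*Protocol article*

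**What the plan says.** Under Statistical analysis, the protocol article states: "All analyses of primary and secondary outcome measures will be conducted as intention-to-treat analyses (ITT". It continues: "Depending on the amount of drop-out, the ITT analyses will be carried out either as mixed models or using the" LOCF method. It gives no level of drop-out that decides between the two.

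The same section takes clinically significant change on the LSAS-SR, SIAS and SPS at post-treatment and follow-up. There, "we will calculate the proportion of improved and recovered participants using the Reliable Change Index" together with Jacobson and Truax cut-off c. It does not say how a participant with a missing score is classified.

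The schedule is in Recruitment and procedure. Outcome questionnaires are completed at Week 0, at the end of Week 2, at the end of Week 11 and four months after the intervention. The attention or control training fills Weeks 1 and 2. The nine CBT modules fill Weeks 3 to 11.

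The Abstract gives this measure weight, since adding attention training "could increase the proportion of participants who improve and recover through Internet-based self-help".

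**The concern.** Improved and recovered are statuses of individuals, so each participant needs a score at the time point in question. No outcome questionnaire is planned between the end of Week 2 and the end of Week 11, which is the whole CBT period. LOCF at Week 11 can therefore only bring forward a Week 2 or a Week 0 score:

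- **Week 0 carried forward:** change is exactly zero, and the participant cannot be classed as improved.
- **Week 2 carried forward:** the participant is classed on the effect of the training alone, while the result is labelled as the outcome of training plus CBT.

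The arm with more missing Week 11 scores will then tend to show a lower responder proportion even if the treatments do equally well. The mixed-model branch estimates means without filling in individual scores, so a further rule is needed before anyone with a missing score can be classified. The responder measure may thus depend on which branch is taken, and that choice depends on how much drop-out there turns out to be. At stake is the measure that the article itself uses to motivate the trial.

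**Working it through.** **1. The plan's own figure.** Sample size assumes d = 0.50, two-sided α = 0.05 and 80% power, and N "will be set at 128 participants, with 64 participants in each group". The normal approximation gives 63 per arm. The exact t-test gives 63.77, rounded up to 64 per arm, with power of 80.1% at 64. The 128 is reproduced. It is not in dispute and serves here only as the denominator.

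**2. Which score LOCF uses.**

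| Missing at | Last available score | Before or after CBT |
|---|---|---|
| Week 11 | Week 2, or Week 0 if Week 2 is also missing | Always before |
| 4 months, Week 11 present | Week 11 | After |
| 4 months, Week 11 also missing | Week 2 or Week 0 | Before |

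**3. Inputs for the illustration.**

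- p = share improved at Week 11, taken as the same in both arms and the same for those missing had they been measured. Range 50% to 65%, borrowed from the Background, where it describes earlier internet CBT trials.
- q = share classed as improved on a carried-forward score. Assumed 0% to 10%; it is exactly 0 for a carried-forward Week 0 score.
- d = share missing Week 11. The article gives none. Assumed 10%, 20% and 30%, that is 6.4, 12.8 and 19.2 of 64.

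**4. Proportion within one arm.** LOCF proportion = (1 − d)p + dq.

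| d | p = 50%, q = 0 to 10% | p = 65%, q = 0 to 10% |
|---|---|---|
| 10% | 45% to 46% | 58.5% to 59.5% |
| 20% | 40% to 42% | 52% to 54% |
| 30% | 35% to 38% | 45.5% to 48.5% |

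**5. False difference between arms when the true difference is zero.** Subtracting one arm from the other gives (d2 − d1)(p − q).

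- 10% versus 20% missing: smallest 0.10 × (0.50 − 0.10) = 4 points; largest 0.10 × (0.65 − 0) = 6.5 points.
- 10% versus 30% missing: smallest 0.20 × (0.50 − 0.10) = 8 points; largest 0.20 × (0.65 − 0) = 13 points.

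**6. Scale.** With 64 per arm, the standard error of a difference in proportions is √(2 × 0.50 × 0.50 / 64) = 8.8 points at p = 50% and √(2 × 0.65 × 0.35 / 64) = 8.4 points at p = 65%. The false difference is then 4/8.8 = 0.5 to 6.5/8.4 = 0.8 standard errors in the first case, and 8/8.8 = 0.9 to 13/8.4 = 1.5 in the second. With equal missing rates in the two arms and the same p and q, it is zero, and only the level of both proportions falls.

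**The case against.** Several points count on the other side.

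- **A condensed article may leave detail to a full plan.** The drop-out threshold and the rule for a missing responder may be set out there. That stands, and their absence is not the point. LOCF, however, is stated as a permitted method, and the stated schedule fixes which score it would use.
- **The ITT sentence may not reach these proportions.** Outcome measures lists the composite, the MADRS-S and the Quality of Life Inventory, and clinically significant change is not on that list. This is a fair doubt, although the three scales classified are the components of the primary composite.
- **Stopping treatment is not the same as a missing score.** Week 11 questionnaires are to be collected however much of the programme was done. This limits how many people are affected, not how they are classified. The Mini-SPIN does not fill the gap, because it is given before training sessions, which end with Week 2.
- **A carried-forward baseline amounts to not improved**, the same rule proposed below as a sensitivity analysis. That is true for Week 0 scores. It is acceptable as a labelled sensitivity analysis, less so as an unlabelled part of the main result, and Week 2 scores do not follow it.

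Two stronger readings are tempting but not supported. A reader might infer that the mixed-model branch rules out ITT proportions and must yield completer rates. The article does not say that participants with missing scores are left out, and ITT proportions remain available through imputation, a missing-equals-not-improved rule or a repeated-measures model for the binary status. A reader might also infer that the plan hides harm, because only improved and recovered participants are counted while the active arm is trained towards threat. The Background statement that "greater attention-bias scores prior to the intervention were associated with higher post-treatment anxiety scores in CBT" concerns bias before treatment as a predictor, not an effect of training. The same section reports that patients benefited most from training towards negative cues.

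**Conclusion.** The concern holds in a limited form. If LOCF is applied to the improved and recovered proportions, everyone missing Week 11 is classified at post-treatment on a pre-CBT score. At 4 months this is so only for those who also lack Week 11. The mixed-model branch gives no individual scores for participants with missing data, so the two permitted branches need not give the same responder measure.

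The size depends on assumptions. The article gives no drop-out rate, q is assumed, and p is taken from earlier trials and held equal for observed and missing participants. On that basis, a gap of 10 percentage points in missing rates produces a false difference of 4 to 6.5 points, and a gap of 20 points one of 8 to 13 points. If those missing truly did worse, part of the difference would be real. The absence of a deterioration count is an omission that could usefully be filled, not an error.

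**What to change.** Remove the LOCF option for the improved and recovered proportions. Multiply impute missing Week 11 and 4-month LSAS-SR, SIAS and SPS scores, separately by arm, using all four assessments (Week 0, Week 2, Week 11 and 4 months). In each imputed data set, classify all randomised participants with the Reliable Change Index and cut-off c, then combine the proportions across sets. Repeat with missing counted as not improved as a sensitivity analysis.

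The cost is a little more analysis work and no new data. The resulting rates may look less favourable than rates among participants with complete data. A reliably deteriorated category could be reported from the same index at no further cost; it is an optional addition.

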The stimuli will consist of images from 62 men and 62 women, each showing three different facial expressions: positive (happiness), neutral, and negative (disgust), as well as of 111 positive words, 111 neutral words, and 111 negative words. Both the faces and the words are centered on the screen with the faces 4 pixels and the words 180 pixels apart. The stimuli material will be taken from the Umeå University Database of Facial Expressions [61], the Karolinska Directed Emotional Faces [62] and the Matsumoto and Ekman’s Japanese and Caucasian Facial Expressions of Emotion [63].

In the treatment condition, the probe will always be at the same location as the more negative stimulus in the pair. In contrast, in the placebo condition the probe appears randomly, with equal frequency in the two positions. The intervention will consist of 14 sessions of either treatment or placebo exercises. As shown in Table 1, each session will encompass 192 trials.

**Table 1 T1:** Number of trials per probe position per session depending on condition including assessment phase

	**Trials per session**	**Length of stimulus display, ms**	**positive - ****neutral**	**positive - ****negative**	**neutral - ****negative**	**positive****- neutral**	**positive****- negative**	**neutral****- negative**
**Bias assessment**	96	500 (faces)	8	8	8	8	8	8
		500 (words)	8	8	8	8	8	8
**Control training**	192	500 (faces)	8	8	8	8	8	8
		500 (words)	8	8	8	8	8	8
		1000 (faces)	8	8	8	8	8	8
		1000 (words)	8	8	8	8	8	8
**Attention training**	192	500 (faces)	16	16	16	-	-	-
		500 (words)	16	16	16	-	-	-
		1000 (faces)	16	16	16	-	-	-
		1000 (words)	16	16	16	-	-	-

Underlined words indicate the position of the probe.

The attention bias will be assessed in two additional sessions, one before (day 0) and one after (day 15) the training. The attention-bias assessment includes 96 dot-probe trials similar to those of the training sessions, with the cue presented for 500 ms. The probe will appear with equal frequency at the location of neutral, negative, and positive cues (see Table 1).

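### The attention-bias ANOVA is in effect a change-score test: valid, but less precise than the baseline-adjusted ANCOVA the protocol already uses for its clinical outcomes

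*Protocol article*

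**What the plan says.** The protocol article, Statistical analysis, sets the bias test as follows: "To examine changes in attention bias, we will conduct a 2 (pre-assessment/post-assessment", with arm and cue valence as the other two factors of a 2x2x2 ANOVA. It then defines a bias score: "We will calculate this bias score by subtracting the mean reaction times to negative cues from the mean reaction times to positive cues". It adds that "we will analyze changes in the attention bias from pre- to post-assessment on an individual level using an attention bias score", without naming a model for comparing the arms.

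The clinical outcomes are treated differently in the same section. Between-group differences on the social anxiety composite and "on secondary outcome measures will be calculated using analysis of covariance (ANCOVA), with pre-treatment scores as the covariate".

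The baseline needed for such an adjustment is scheduled. Under Attention training and control training: "The attention bias will be assessed in two additional sessions, one before (day 0) and one after (day 15) the training". Under Recruitment and procedure, a 96-trial bias task is also part of the screening battery, before randomisation.

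The Outcome measures section makes the social anxiety composite primary, and the MADRS-S and the Quality of Life Inventory secondary. Attention bias is in neither list. The article gives no SD, expected effect, pre-post correlation or power for it.

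**The concern.** The training is meant to work by changing how participants attend to threat, and the bias analysis is the check on whether it did so. That check compares raw change between arms, which subtracts the whole baseline score instead of the share that predicts the later score. When the measure is noisy, this adds baseline noise to the comparison.

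The bias score is a difference of two mean reaction times, so a participant's stable overall speed cancels and trial-to-trial noise remains. A low to moderate pre-post correlation is therefore plausible, and that is where a change score loses most. At stake is the precision of the mechanism check. A wide interval for the effect on bias makes it harder to tell a training that did not shift attention from one whose shift was missed.

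**Working it through.** **Inputs.** From the article: 64 per arm, two-sided alpha 0.05, d = 0.50, power 80% (Sample size, set for the clinical comparison); bias assessed on day 0 and day 15 with 96 trials each time (Attention training and control training, Table 1). Assumed, because not given: the pre-post correlation r of the bias score, equal SDs s at both times, and a 0.5 SD effect on bias for illustration only.

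**The plan's own figure.** A two-sided t-test with d = 0.50, alpha 0.05 and 80% power needs 63.77, so 64 per arm and 128 in all. Power at 64 per arm is 80.1%. The stated sample size reproduces.

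**Step 1: what the ANOVA tests.** For one participant, let B be the mean reaction time to positive cues minus that to negative cues. The time by cue contrast is B(day 15) − B(day 0), the change in the bias score. Comparing this contrast between two arms is the three-way interaction, so its F equals the square of the two-sample t on change. On one simulated data set both were 6.4057.

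**Step 2: variances.**
- Change score: 2(1−r)s².
- ANCOVA (large samples): (1−r²)s².
- Ratio, change to ANCOVA: 2(1−r)/[(1−r)(1+r)] = 2/(1+r).
- Post-training score alone: s². The change score is worse than this when 2(1−r) > 1, that is, when r < 0.5.

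**Step 3: numbers.** Power is for a two-sample t-test at 64 per arm, with standardised effect 0.5/√(variance/s²).

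| r | Change variance / s² | ANCOVA variance / s² | ANCOVA saving | Power, planned test | Power, ANCOVA |
|---|---|---|---|---|---|
| 0.1 | 1.80 | 0.99 | 45% | 55% | 80–81% |
| 0.2 | 1.60 | 0.96 | 40% | 60% | 82% |
| 0.3 | 1.40 | 0.91 | 35% | 66% | 84% |
| 0.5 | 1.00 | 0.75 | 25% | 80% | 90% |
| 0.7 | 0.60 | 0.51 | 15% | 95–96% | 98% |
| 0.8 | 0.40 | 0.36 | 10% | 99% | over 99% |
| 0.9 | 0.20 | 0.19 | 5% | over 99% | over 99% |

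Where two values are shown, they are the t and normal calculations. Simulation with 4,000 runs per value gave ANCOVA-to-change variance ratios of 0.66, 0.75 and 0.90 at r = 0.3, 0.5 and 0.8, against 0.65, 0.75 and 0.90 from the formula.

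**Step 4: which r is plausible.** Each mean rests on at most 96/2 = 48 trials before exclusions. Suppose a trial SD of 100 to 150 ms and a stable true bias with SD 10 to 20 ms (all assumed). The noise variance of the score is 2 × 100²/48 = 417 to 2 × 150²/48 = 938 ms². Then r runs from 100/(100+938) = 0.10 to 400/(400+417) = 0.49.

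**Step 5: unequal SDs.** At r = 0.5 with the post SD 1.5 times the pre SD, the ratio is (1 + 2.25 − 1.5)/(2.25 × 0.75) = 1.75/1.69, about 1.04, so the gain almost vanishes. With a post SD 0.75 times the pre SD, it is 0.8125/0.4219, about 1.93.

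**The case against.** The strongest reply is that nothing here is wrong. The ANOVA is unbiased under randomisation, bias is not a listed outcome, the stated hypothesis concerns social anxiety, and the sample was sized for the clinical comparison. The size of the gain also rests on an r that the article does not give: at 0.8 or above the saving is 10% or less, and a larger post-training SD would shrink it further. All of this stands. It makes the point one of efficiency and keeps the gain conditional. It does not explain why the same section adjusts for baseline elsewhere but not here. The extra individual-level analysis does not close the gap either, since no model for it is named.

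Two stronger readings are tempting, and the document supports neither.

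- A reader might infer that a null clinical result could not be interpreted. The randomised clinical comparison answers the trial's question whatever the bias test shows. A change-score estimate with its confidence interval still informs on the training's effect, only less precisely.
- A reader might infer a missing-data fault, because the ANOVA needs both sessions and the rule "All analyses of primary and secondary outcome measures will be conducted as intention-to-treat analyses (ITT") does not reach attention bias. But the baseline task is part of screening. If that is the day-0 assessment, every randomised participant should have it. Both methods then mainly lose the people without a day-15 session.

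**Conclusion.** The point holds as a matter of efficiency. The planned interaction test is a valid change-score comparison that forgoes precision available from data already collected. The saving is about 25% to 45% of the variance if r lies between 0.5 and 0.1, which the construction of the score makes plausible but the article does not establish. At high r it is minor. Below r = 0.5 the planned test is less precise than comparing post-training scores alone. These figures assume equal pre and post SDs, and the power values also borrow a 0.5 SD effect for illustration. The supportable consequence is a less precise check of whether the training moved attention.

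**What to change.** In Statistical analysis, make the between-arm test for attention bias an ANCOVA of the day-15 bias score on arm, adjusted for the day-0 bias score, and report the adjusted difference with its confidence interval. Keep the 2x2x2 ANOVA and its cell means as descriptive or supportive. This changes one sentence. It needs no new data or visits, because both assessments are already scheduled.
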